## Abstract

**Background:** Anxiety is one of the most frequent disorders during the perinatal stage that is associated with adverse health effects in women and their babies. In spite of this, preventive interventions during this stage are scarce. A long-distance intervention carried out during pregnancy can be an effective and accessible resource to help improve women’s emotional state. The objective of this study is to present and assess the effectiveness of a telepsychology cognitive–behavioral preventive intervention during pregnancy to manage anxiety. **Methods:** A random clinical trial will be carried out among pregnant women in Spain. The psychological intervention will take place via videoconference in seven weekly sessions, lasting one hour each, with groups of 6–8 pregnant women. Study outcomes will be collected via online questionnaires at five points in time: pre-intervention (baseline: t0), post-intervention (baseline: t1), follow-up at 1 month (t2), follow-up at 3 months (t3) and follow-up at 6 months (t4). The control group will receive usual pregnancy care (attendance at pregnancy follow-up consultations and information and answers to frequently asked questions provided by the midwife). Our primary hypothesis is that the intervention will decrease the frequency of women who present anxious symptomatology during pregnancy. The second objective is to analyze the effectiveness of this intervention to prevent depressive symptomatology during pregnancy, as well as postpartum anxiety and depressive symptomatology. The primary outcome measure is the difference in the mean anxiety score between the intervention and control groups assessed by the Edinburgh Depression Scale-Anxiety Subscale (EDS-3A), the State–Trait Anxiety Inventory (STAI) and Generalized Anxiety Disorder Screener (GAD-7) at the end of the intervention and at 1, 3 and 6 months postpartum. Generalized anxiety disorder (GAD) will be evaluated with the SCID clinical interview at the same time points. The secondary outcome will be determined by using the EPDS at the same time points. **Conclusions:** The results will determine whether a cognitive behavioral therapy applied via videoconference is well accepted by pregnant women, and if it is effective in preventing anxiety and emotional symptoms during the perinatal stage. If this intervention is an effective and useful resource among pregnant women, it can be implemented as a tool in Spanish healthcare.

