On the other hand, it is worth remembering the high comorbidity of anxiety and depression. In a review and meta-analysis whose objective was to evaluate the effectiveness of psychological interventions to reduce perinatal anxiety, it was found that psychological interventions aimed at reducing anxiety during the perinatal stage were also effective in reducing symptoms of depression [7]. This supports research suggesting that transdiagnostic interventions targeting both anxiety and depressive symptoms tailored to the perinatal period may be more beneficial than disorder-specific interventions [37] and indicates the need to create transdiagnostic interventions to address symptoms of anxiety and depression in women during the perinatal stage since these comorbidities are generally not recognized or treated [41]. Therefore, considering the high frequency with which anxiety and depression occur together, treatments should treat them simultaneously [26].

To date, there is no protocol in Spain to prevent anxiety and comorbid emotional symptomatology during the perinatal stage by means of a videoconference psychological intervention. An intervention of this type could facilitate access and be helpful to many women during this period, reducing levels of anxiety and comorbid emotional symptoms.

The primary objective of the current study is to determine whether a preventive psychological intervention is superior to the usual care during pregnancy (attendance at pregnancy follow-up consultations and information and answers to frequently asked questions provided by the midwife) to prevent anxiety symptoms during pregnancy. The secondary objective is to examine whether this same intervention is more effective than usual care in preventing depressive symptoms during pregnancy, as well as anxiety and depressive symptoms postpartum.

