### 2.3. Outcomes and Allocation of Participants to Trial Groups

#### 2.3.1. Primary Outcome

The primary outcome measure will be the difference in the mean anxiety scores between the intervention and control groups assessed by the EDS-3A, STAI and GAD-7 questionnaire before and at the end of the intervention, and one month, 3 months and 6 months after the intervention. Generalized anxiety disorder (GAD) will also be evaluated through the DSM-5 clinical interview at the same time points. In this case, the percentages found will be compared.

The Edinburgh Depression Scale-Anxiety Subscale (EDS-3A) is the anxiety subscale of the Edinburgh Postnatal Depression Scale (EPDS) [42]. Different studies, e.g., [43,44] have found that three items (3, 4, 5) can detect anxiety in women during the perinatal period. Each of the three items has four response options (0 = none, 1 = somewhat, 2 = quite a bit, and 3 = a lot). The total score of the subscale ranges from 0 to 9. The cut-off point used in the EDS-3A to detect anxious symptomatology will be ≥5 [45].

The State–Trait Anxiety Inventory (STAI) [46] assesses both the current level of anxiety and the individual’s predisposition to suffering from anxiety. It consists of 40 items, 20 of which refer to the state subscale (STAI-E), with the other 20 referring to the trait subscale (STAI-R). The score for each subscale ranges from 0 to 60, with higher scores indicating higher levels of anxiety. In this case, the State Anxiety Subscale (STAI-E) will be applied; the recommended cut-off point for women is greater than 31 (75th percentile).

Generalized Anxiety Disorder Screener (GAD-7) [47] is a self-administered instrument consisting of seven items with four response options. The total score ranges from 0 to 21, with the highest scores being the most severe. The GAD-7 has been validated for use in Spanish-speaking pregnant women [48]. The cut-off point used to detect anxiety symptoms will be ≥7 [49].

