#### 2.3.2. Secondary Outcome

The secondary outcome measure will be the difference in the mean scores between groups on the EPDS at the same time periods described above. Depressive symptoms will be assessed using the EPDS [42], which is a self-reported questionnaire consisting of 10 items with four response options. The scores range between 0 and 30, with higher scores indicating greater severity of depression. The Spanish validation of the EPDS for use in pregnancy will be used [51]. The most appropriate cut-off point for screening for probable antenatal depression has been determined to be 10.

Additionally, acceptability and satisfaction with the program will also be evaluated through a satisfaction questionnaire.

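### The primary outcome includes anxiety at postpartum visits and names no pregnancy visit as primary, although the primary objective is anxiety during pregnancy

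*Protocol article*

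**What the plan says.** The objectives are divided by period. The Introduction gives the primary objective as superiority over usual care "to prevent anxiety symptoms during pregnancy", and the secondary objective as "preventing depressive symptoms during pregnancy, as well as anxiety and depressive symptoms postpartum". The abstract's primary hypothesis has the same period: "the intervention will decrease the frequency of women who present anxious symptomatology during pregnancy".

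The outcomes are divided by construct instead. Section 2.3.1 makes the group difference in mean EDS-3A, STAI and GAD-7 scores the primary outcome, measured "before and at the end of the intervention, and one month, 3 months and 6 months after the intervention". The first paragraph of section 2.8 carries all five assessments into the primary analysis. Section 2.3.2 reads "The secondary outcome measure will be the difference in the mean scores between groups on the EPDS" and adds only a satisfaction questionnaire.

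The abstract times the primary outcome differently: "at the end of the intervention and at 1, 3 and 6 months postpartum". Sections 2.1, 2.3.1 and 2.8 count the follow-ups from the end of the intervention, not from birth.

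**The concern.** An outcome labelled primary should address the primary objective. Here one primary outcome covers two periods that the protocol ranks differently, and nothing says which visit carries the primary claim. Postpartum anxiety has a secondary objective but no secondary outcome; it appears only inside the primary one.

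What is at stake is the meaning of a positive trial. If the groups differed only at visits after birth, the protocol as written would allow that to be reported as success on the primary outcome, while the question of anxiety in pregnancy stayed unanswered. The Bonferroni adjustment in section 2.8 does not settle this. It limits error across comparisons but does not decide which period the primary claim concerns.

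**Working it through.** **Inputs**
- Gestational age at entry: at most 16 (section 2.4; the unit is not printed, weeks assumed). The lower end is not given; 8 weeks is assumed.
- Delay from baseline to the first session: 4–6 weeks (section 2.1).
- Seven weekly sessions (section 3.2): 6 weeks from first to last, up to 7 allowed.
- t1 is taken at session 7 (section 3.2). The control group is assumed to be assessed at the same time.
- t2, t3 and t4: 1, 3 and 6 months later, taken as 4.3, 13.0 and 26.1 weeks.

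**Methods timing**

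Gestational week at visit = entry + delay + sessions + follow-up interval.
- t1 = entry + (4 + 6) to (6 + 7) = entry + 10 to 13
- t2 = entry + 14.3 to 17.3
- t3 = entry + 23.0 to 26.0
- t4 = entry + 36.1 to 39.1

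| Visit | Entry at week 8 | Entry at week 16 | Period |
|---|---|---|---|
| t1 | 18–21 | 26–29 | pregnancy |
| t2 | 22–25 | 30–33 | pregnancy |
| t3 | 31–34 | 39–42 | mixed |
| t4 | 44–47 | 52–55 | postpartum |

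**Where birth falls**
- t4, fastest schedule, birth at week 40: postpartum if entry is later than 40 − 36.1 = 3.9 weeks. With birth at week 42: later than 42 − 36.1 = 5.9 weeks. On the slowest schedule the thresholds are lower still (0.9 and 2.9 weeks). So t4 is postpartum for practically everyone.
- t3, birth at week 40: on the slowest schedule it is postpartum if entry is later than 40 − 26.0 = 14.0 weeks. On the fastest schedule entry would have to be later than 40 − 23.0 = 17.0 weeks, which section 2.4 excludes. With birth at week 37 the thresholds drop to 11.0 and 14.0 weeks. So t3 is mixed.
- t2 is at week 33 at the latest, before any birth at week 37 or later.

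**Abstract's timing**

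t1 is unchanged. t2, t3 and t4 are postpartum by definition, which is three of the four post-baseline visits.

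**Objectives against outcomes**

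| Objective (Introduction) | Where it is measured |
|---|---|
| Primary: anxiety in pregnancy | Section 2.3.1, together with all later visits |
| Secondary: depressive symptoms, pregnancy and postpartum | Section 2.3.2, EPDS |
| Secondary: anxiety postpartum | Not in section 2.3.2; only within 2.3.1 |

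The EPDS contains the three EDS-3A items, but section 2.3.2 uses its score for depressive symptoms, so it does not fill the last row.

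**Sample size**

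For d = 0.55, two-sided α = 0.05 and 80% power, the normal approximation gives 2 × (1.96 + 0.84)² / 0.55² ≈ 52 per group. The two-sample t-test gives 52.87, rounded up to 53, as in section 2.7. This is a single two-group comparison tied to no visit, so naming one visit as primary leaves it at 53.

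**The case against.** A reader might infer that the primary result cannot answer the primary question at all, or that an effect in pregnancy must be diluted by averaging it with postpartum visits. The protocol supports neither reading. Section 2.8 plans Cohen's d at each follow-up time, post hoc comparisons between visits, and comparison of GAD frequencies at each assessment. It states no time-averaged group effect. A repeated-measures analysis can show an effect that is present in pregnancy and fades after birth, and estimates at t1 (and at t2 on the Methods timing) will exist. Any figure for dilution would need an averaged estimand that the plan does not specify.

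It can also be said that this is mostly labelling. Outcomes are grouped by construct and objectives by period, and no data are lost. That is fair as to practical harm, and it is why the remedy is wording only. A further argument is that the real defect is the clash between counting follow-up from birth and counting it from the end of the intervention. That clash has to be resolved first, but postpartum visits are in the primary outcome under either timing.

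The objection leaves the designation itself untouched. All visits are expressly placed in the primary outcome and the primary analysis, so this is a conflict with the stated objectives and not a detail left to an analysis plan.

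**Conclusion.** The mismatch holds. As defined, the primary result does not isolate pregnancy, and a difference confined to the postpartum visits could be claimed as primary success. At least one of the four post-baseline visits (t4) is postpartum for practically every woman on the Methods timing, with t3 mixed; on the abstract's timing it is three of four. The claim goes no further than that: estimates in pregnancy are planned, but none is named as the primary one.

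This rests on gestational age being in weeks, entry from about week 8, and birth between weeks 37 and 42. The assumed lower bound matters little for t4, which is postpartum for any entry later than about week 6 even with birth at week 42. The point concerns only the period of the primary outcome, not the number of anxiety scales or tests.

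**What to change.** 1. Reconcile the abstract's postpartum timing with sections 2.1, 2.3.1 and 2.8, which count from the end of the intervention.
2. In sections 2.3.1 and 2.8, name t1 as the primary time point for the between-group anxiety comparison. It falls in pregnancy under both timings.
3. In section 2.3.2, list anxiety at t2, t3 and t4 as secondary outcomes for all participants. t4 serves the postpartum objective, as do t2 and t3 if the abstract's timing stands. Do not assign t3 by whether a woman has already given birth: that would sort participants by an event after randomisation and make t3 a secondary outcome for only some of them.
4. Align the abstract's primary outcome sentence, and the registry entry if it carries the same definition.

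The cost is wording. No visit is added or moved, and the 53 per group is unaffected. The downside is that the primary claim covers a shorter period and the later anxiety results carry secondary status.

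### The only depression outcome, the EPDS total, contains the primary EDS-3A anxiety score, so an EPDS difference alone does not show an effect on the non-anxiety depressive items

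*Protocol article*

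**What the plan says.** Section 2.3.1 (Primary Outcome) compares mean anxiety scores between groups, "assessed by the EDS-3A, STAI and GAD-7 questionnaire before and at the end of the intervention" and at three later follow-ups. It states that the EDS-3A "is the anxiety subscale of the Edinburgh Postnatal Depression Scale (EPDS", that "three items (3, 4, 5) can detect anxiety in women during the perinatal period", and that "The total score of the subscale ranges from 0 to 9".

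Section 2.3.2 (Secondary Outcome) states: "The secondary outcome measure will be the difference in the mean scores between groups on the EPDS at the same time periods described above". It describes the EPDS as a scale "which is a self-reported questionnaire consisting of 10 items with four response options", scored 0 to 30, and reads higher totals as more severe depression. The article names no other measure of depressive symptoms.

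The secondary objective, at the end of the Introduction, is "to examine whether this same intervention is more effective than usual care in preventing depressive symptoms during pregnancy", together with anxiety and depressive symptoms after birth. Section 2.8 (Analysis Plan) gives depressive symptoms the same kind of analysis as the primary scores. The article does not mention a score without the shared items, or the overlap as a matter for interpretation.

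**The concern.** The same three answers enter the trial twice: once as primary evidence on anxiety, and again as part of the secondary evidence on depression. The programme is aimed at anxiety, so movement in these three items is what the trial hopes to see. Any such movement lowers the EPDS mean by the same number of points, even if none of the other seven items changes.

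At stake is how an EPDS result is read. A lower EPDS mean in the intervention group would naturally be reported as prevention of depressive symptoms, and as support for the transdiagnostic rationale in section 3.1. The planned analysis cannot show whether the difference comes from the anxiety items, from the other items or from both. Nor would agreement between the EDS-3A and the EPDS be two independent pieces of evidence, because one score is contained in the other.

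**Working it through.** **Inputs from the article**
- EDS-3A: EPDS items 3, 4 and 5, range 0-9 (section 2.3.1).
- EPDS: 10 items, range 0-30 (section 2.3.2).
- Planning effect d = 0.55, α = 0.05, 80% power, 53 per group, recruitment target 140 (section 2.7).
- Allocation 2:1 (section 2.2).

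**Inputs assumed**
- SD of the EDS-3A 1.8-2.3 and SD of the EPDS total 4.5-5.5. The article gives no SDs.
- An effect of d = 0.55 on the EDS-3A and none on the other seven items. This is a limiting case chosen to isolate the overlap. Section 2.7 does not tie the 0.55 to the EDS-3A.

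**The plan's own figure.** A two-sample t-test, two-sided, with d = 0.55, α = 0.05 and 80% power needs 52.87 per group, so 53. The stated figure reproduces.

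**Shared content.** 3 of 10 items, and 9/30 = 30% of the score range. The remaining seven items run from 0 to 7 × 3 = 21.

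**How an anxiety-only effect passes into the total.** Write EPDS = A + B, with A the EDS-3A and B the other seven items. If the effect is on A alone, the mean difference on the EPDS equals the mean difference on A:
- raw difference = 0.55 × SD(A) = 0.55 × 1.8 = 0.99 to 0.55 × 2.3 = 1.265, about 1.0-1.3 points;
- d on the EPDS = 0.55 × SD(A) / SD(EPDS), from 0.55 × 1.8 / 5.5 = 0.18 to 0.55 × 2.3 / 4.5 = 0.28.

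**Numbers analysed.** Going from 140 to 2 × 53 = 106 implies a loss of 1 − 106/140 = 24.3%. At 2:1, 106 women are about 70/35. With no loss, 140 are about 93/47.

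**Chance of p<0.05 on the EPDS total at one time point (two-sided t-test)**

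| SD EDS-3A | SD EPDS | d on EPDS | 70/35 | 93/47 |
|---|---|---|---|---|
| 1.8 | 5.5 | 0.18 | 14% | 17% |
| 1.8 | 4.5 | 0.22 | 18% | 23% |
| 2.3 | 5.5 | 0.23 | 20% | 25% |
| 2.3 | 4.5 | 0.28 | 27% | 35% |

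**Sensitivity to the assumptions.** Two other sets were tried: SD(A) = 2 with SD(B) = 2 to 4 and a correlation of 0.3-0.7 between A and B; and ten equal-variance items with inter-item correlation 0.2-0.5. Together they give d of about 0.18-0.34 on the EPDS, and p<0.05 in about 17-47% of trials with 93/47 analysed. The direction is the same and the upper end is higher.

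**What the percentages mean.** In this scenario the groups truly differ on the mean EPDS, so rejecting that null is correct. The percentages show how often a significant EPDS result would arise with no change in the seven non-anxiety items. They are not false-positive rates to set against 5%.

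**The case against.** The case for leaving the plan alone has five parts.

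- **The EPDS total is a legitimate outcome.** Section 2.3.2 uses the Spanish validation for pregnancy, and section 2.3.1 openly says where the EDS-3A comes from. No statement is false. This stands, and it is why the total should stay.
- **The objective does not ask for an effect separate from anxiety.** The Introduction and section 3.1 stress comorbidity and treating both together, and the programme includes behavioural activation and cognitive restructuring, so zero effect on seven items is an extreme case. This stands as a limit on the illustration. It does not remove the ambiguity, because depressive symptoms are named as a target of their own and the total cannot show which items moved.
- **A condensed article may leave a supportive analysis to the statistical analysis plan.** Also fair: its absence here is not an error in itself. The point rests on what the article does fix, namely the sole depression measure and its reading as severity of depression.
- **A seven-item sum is not the validated score and has no cut-off.** Correct. It should support interpretation and not act as a strict gate.
- **Only one of three primary scales overlaps.** Correct. The STAI-E and GAD-7 share no stated items with the EPDS. That protects the anxiety conclusions but does nothing for the depression conclusion, which rests on the EPDS alone.

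A reader might go further and infer that any anxiety effect will show up as a depression effect, or that the secondary objective cannot be answered. The article supports neither. The effect is diluted, and under the main assumptions most such trials would show no significant EPDS difference. The other seven items are on the same form and can be analysed.

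**Conclusion.** The point holds as a matter of construct interpretation, and its label is cheap improvement. The nesting is a fact of the article: 30% of the EPDS range is the EDS-3A. A difference on the EPDS total alone therefore does not show an effect on the non-anxiety depressive items, and the EDS-3A and EPDS results must not be presented as independent confirmation of each other.

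The size is illustrative only. The figures of d about 0.18-0.28, and p<0.05 in 14-27% (70/35) or 17-35% (93/47) of trials, rest on assumed SDs and on an effect confined to three items. The qualitative conclusion needs neither assumption.

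The reach is narrow. The STAI-E, GAD-7 and diagnostic interview results are unaffected, so the postpartum anxiety part of the secondary objective can still be addressed through them. It would be wrong to read this as an inflated type I error, or as a fault in the primary anxiety analysis.

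**What to change.** Keep the EPDS total as the secondary outcome. In sections 2.3.2 and 2.8:

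- prespecify, as a supportive analysis, the same between-group comparison for the EPDS without items 3, 4 and 5 (seven items, range 0-21) at each time point;
- report its mean difference and confidence interval beside those of the total;
- state that the EDS-3A items are part of the EPDS total and that the two results are not independent;
- say that an EPDS effect will not be described as distinct from anxiety when the seven-item result does not point the same way.

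Judge the seven-item result by its direction and interval. No power has been worked out for it, so a non-significant result should not be read as no effect.

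The cost is a few sentences and one extra analysis of data already collected. The downside is that the seven-item sum is not the validated score and has no cut-off. Fixing it before results are seen avoids a post hoc choice.

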#### 2.3.2. Secondary Outcome

The secondary outcome measure will be the difference in the mean scores between groups on the EPDS at the same time periods described above. Depressive symptoms will be assessed using the EPDS [42], which is a self-reported questionnaire consisting of 10 items with four response options. The scores range between 0 and 30, with higher scores indicating greater severity of depression. The Spanish validation of the EPDS for use in pregnancy will be used [51]. The most appropriate cut-off point for screening for probable antenatal depression has been determined to be 10.

Additionally, acceptability and satisfaction with the program will also be evaluated through a satisfaction questionnaire.

